## APPENDIX H: PATIENT CENTRED SERVICES

### SFQ for PARTICIPANTS – INTRODUCTION TO PCS & SOAs (PCS00)

Thank you for participating in this health centre management training! We would appreciate your feedback on the training session you have attended. Please take a moment to answer the following questions. This is **NOT A TEST** and **WE VALUE YOUR OPINION**. Your opinions will help us improve future trainings. There is no need to write your name on this questionnaire.

All responses will be kept strictly confidential. Thank you!

#### GENERAL INSTRUCTIONS TO COMPLETE THIS QUESTIONNAIRE

1. Please use a dark coloured pen to fill out the questionnaire
2. The health worker identity (ID) number is the unique number that was given to you at the start of this PRIME project. When we request you to give your ID number, please fill the boxes as below:

[ 0 | 5 | 1 | 0 ]

You are asked to enter your ID number like this at the top of each page of your questionnaire.

3. In this questionnaire, we ask you to read each question carefully and either write your response, or look at the statements and decide which response is closest to your own opinion. When you have decided, please circle the number in the column under that response. For example:

| Decide how much you agree with the statements below | Strongly agree | Agree | Disagree | Strongly disagree |
|-----------------------------------------------------|----------------|-------|----------|-------------------|
| I learned new ideas today                           | 1              | 2     | 3        | 4                 |

4. If you change your mind and would like to circle a different response, please cross out your original choice and circle the choice that fits your opinion best. For example, if you change your mind and you decide that your answer is 'disagree', cross through the original and circle the new response as below:

| Decide how much you agree with the statements below | Strongly agree | Agree | Disagree | Strongly disagree |
|-----------------------------------------------------|----------------|-------|----------|-------------------|
| I learned new ideas today                           | <del>1</del>   | 2     | 3        | 4                 |

5. When you have completed the questionnaire, please make sure you have completed everything in the following checklist:

|                                                       |                                                                                                                                                                                                                                                                                                                                                                                                                                                             |
|-------------------------------------------------------|-------------------------------------------------------------------------------------------------------------------------------------------------------------------------------------------------------------------------------------------------------------------------------------------------------------------------------------------------------------------------------------------------------------------------------------------------------------|
| For the first time you attend a workshop only: |  [For the first time only] I have signed and dated the consent form
 [For the first time only] I have completed my demographic details form                                                                                                                                                                                                                                                              |
| For every workshop:                            |  I have answered all of the questions in this questionnaire
 I have checked that I have circled the responses that are closest to my opinion
 I have written my health worker ID number on all of the pages of the questionnaire
 I have written my health worker ID number on the envelope and will place this completed form inside the envelope |

**PATIENT CENTRED SERVICES  
SFQ for PARTICIPANTS – INTRODUCTION TO PCS & SOAs (PCS00)**

Health worker ID

[ ] [ ] [ ] [ ]

Today's date

[ ] [ ] / [ ] [ ] / [ ] [ ]  
day month year

**1. Please complete the table below about your learning today by circling the response closest to your opinion.**

| Decide how much you agree with the statements below           | Strongly agree | Agree | Disagree | Strongly disagree |
|---------------------------------------------------------------|----------------|-------|----------|-------------------|
| I learned new ideas today                                     | 1              | 2     | 3        | 4                 |
| I understood everything the trainer taught today              | 1              | 2     | 3        | 4                 |
| I felt the training was relevant to my daily work             | 1              | 2     | 3        | 4                 |
| The ideas I learned today will be useful for me in the future | 1              | 2     | 3        | 4                 |
| I was given a chance to ask all of my questions               | 1              | 2     | 3        | 4                 |
| I felt that the trainer answered all our questions well       | 1              | 2     | 3        | 4                 |
| I felt able to practice new skills in the workshop today      | 1              | 2     | 3        | 4                 |
| I was given a chance to give my opinions                      | 1              | 2     | 3        | 4                 |
| I will recommend my colleagues to attend this training        | 1              | 2     | 3        | 4                 |

**If you have any comments on the above statements, Please write them below:**

**PATIENT CENTRED SERVICES**  
**SFQ for PARTICIPANTS – INTRODUCTION TO PCS & SOAs (PCS00)**

Health worker ID

[ ] [ ] [ ] [ ]

Today's date

[ ] [ ] / [ ] [ ] / [ ] [ ]  
 day month year

**2. Please complete the table below about the skills you have learnt from the training topic, by circling the response closest to your opinion.**

| Decide how much you agree with the statements below | Strongly agree | Agree | Disagree | Strongly disagree |
|-----------------------------------------------------|----------------|-------|----------|-------------------|
| This training helped me to think about              | 1              | 2     | 3        | 4                 |
| This training has helped me to see                  | 1              | 2     | 3        | 4                 |
| This training has given me ideas for how to         | 1              | 2     | 3        | 4                 |
| After this training, I feel able to change          | 1              | 2     | 3        | 4                 |
| After this training, I have found ways to           | 1              | 2     | 3        | 4                 |

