### **5.3.1. Self-filled questionnaires**

Our target is to have one self-filled questionnaire completed by all HFI training participants and trainers for each module. There are 5 trainers and approximately 30 health center staff attending 10 module topics. We will conduct up to 350 self-filled questionnaires.

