**If you have any comments on the above statements, Please write them below:**

**HEALTH CENTRE MANAGEMENT TRAINING  
SFQ for PARTICIPANTS – PHC FUND MANAGEMENT (HCM01)**

Health worker ID

[ ] [ ] [ ] [ ]

Today's date

[ ] [ ] / [ ] [ ] / [ ] [ ]  
day month year

**2. Please complete the table below about the skills you have learnt from the training topic, by circling the response closest to your opinion.**

| Decide how much you agree with the statements below                                                               | Strongly agree | Agree | Disagree | Strongly disagree |
|-------------------------------------------------------------------------------------------------------------------|----------------|-------|----------|-------------------|
| This training helped me to think about accountability                                                             | 1              | 2     | 3        | 4                 |
| This training has helped me to see the importance of budgeting and accounting for the PHC Fund                    | 1              | 2     | 3        | 4                 |
| This training has given me ideas for how to show accountability in my work as an in-charge                        | 1              | 2     | 3        | 4                 |
| After this training, I feel able to change the way I manage PHC Funds at my health centre                         | 1              | 2     | 3        | 4                 |
| After this training, I have found ways to management funds at my health centre using the PHC Fund Management Tool | 1              | 2     | 3        | 4                 |

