**If you have any comments on the above statements, Please write them below:**

## HEALTH CENTRE MANAGEMENT TRAINING

### SFQ for PARTICIPANTS – DRUG SUPPLY MANAGEMENT(HCM02)

Health worker ID

[ ] [ ] [ ] [ ]

Today's date

[ ] [ ] / [ ] [ ] / [ ] [ ]  
day month year

2. Please complete the table below about the skills you have learnt from the training topic, by circling the response closest to your opinion.

| Decide how much you agree with the statements below                                                              | Strongly agree | Agree | Disagree | Strongly disagree |
|------------------------------------------------------------------------------------------------------------------|----------------|-------|----------|-------------------|
| This training helped me to think about my role as an in-charge in the drug distribution system                   | 1              | 2     | 3        | 4                 |
| This training has helped me to see the importance of doing my part to keep the drug distribution system on track | 1              | 2     | 3        | 4                 |
| This training has given me ideas for how to make sure drugs reach my health centre using the ADDAT               | 1              | 2     | 3        | 4                 |
| After this training, I feel able to change the way I manage drugs at my health centre                            | 1              | 2     | 3        | 4                 |
| After this training, I have found ways to complete the Drug Stock Card and Requisition & Issue Voucher           | 1              | 2     | 3        | 4                 |
| Please write any comments on the above statements in this section here:                                          |                |       |          |                   |

3. Please complete the table below about today's overall training by circling the response closest to your opinion.

|                                                                  | Very good | Good | Fair | Poor | Very poor |
|------------------------------------------------------------------|-----------|------|------|------|-----------|
| What is your opinion of the trainer's skills today?              | 1         | 2    | 3    | 4    | 5         |
| What is your opinion of the trainer's attitude today?            | 1         | 2    | 3    | 4    | 5         |
| What is your opinion of the learner's manual you received today? | 1         | 2    | 3    | 4    | 5         |

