**If you have any comments on the above statements, Please write them below:**

**HEALTH CENTRE MANAGEMENT TRAINING  
SFQ for PARTICIPANTS – INFORMATION MANAGEMENT (HCM03)**

Health worker ID

[ ] [ ] [ ] [ ]

Today's date

[ ] [ ] / [ ] [ ] / [ ] [ ]  
day month year

**2. Please complete the table below about the skills you have learnt from the training topic, by circling the response closest to your opinion.**

| Decide how much you agree with the statements below                     | Strongly agree | Agree | Disagree | Strongly disagree |
|-------------------------------------------------------------------------|----------------|-------|----------|-------------------|
| This training helped me to think about                                  | 1              | 2     | 3        | 4                 |
| This training has helped me to see                                      | 1              | 2     | 3        | 4                 |
| This training has given me ideas for how to                             | 1              | 2     | 3        | 4                 |
| After this training, I feel able to change                              | 1              | 2     | 3        | 4                 |
| After this training, I have found ways to                               | 1              | 2     | 3        | 4                 |
| Please write any comments on the above statements in this section here: |                |       |          |                   |
|                                                                         |                |       |          |                   |

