**Please write any comments on the above statements in this section here:**

**3. Please complete the table below about today's overall training by circling the response closest to your opinion.**

|                                                                  | Very good | Good | Fair | Poor | Very poor |
|------------------------------------------------------------------|-----------|------|------|------|-----------|
| What is your opinion of the trainer's skills today?              | 1         | 2    | 3    | 4    | 5         |
| What is your opinion of the trainer's attitude today?            | 1         | 2    | 3    | 4    | 5         |
| What is your opinion of the learner's manual you received today? | 1         | 2    | 3    | 4    | 5         |
| What is your opinion of the flip charts that were used today?    | 1         | 2    | 3    | 4    | 5         |
| Overall, what is your opinion of the training today?             | 1         | 2    | 3    | 4    | 5         |

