| 5. Employment
0 = Not employed      2 = Commercial farmer      77 = Other
1 = Teacher      3 = Brew alcohol
2 = Nurse      4 = Market vendor
3 = Member of village health team      5 = Shop keeper      88 = Don't know
1 = Peasant farmer      6 = Transport(Driver/rider)      99 = Refused to answer |                                                             |

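### On 7 of the 10 trainee questionnaires the five topic-skill statements are unfinished, and Appendix N gives caregiver employment codes 1, 2 and 3 two meanings each

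*Supplement*

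**What the plan says.** Section 5.3.1 sets the scope: "There are 5 trainers and approximately 30 health center staff attending 10 module topics", hence "We will conduct up to 350 self-filled questionnaires". Ten trainee forms are printed to match: HCM01 to HCM03 (Appendix D), fever case management (Appendix F) and PCS00 to PCS05 (Appendix H).

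The nine HCM and PCS trainee forms share one layout: nine learning statements, five topic-skill statements and five overall ratings. In HCM01 the skill block is complete ("This training helped me to think about accountability"), and so is the one in HCM02 ("This training helped me to think about my role as an in-charge in the drug distribution system"). In HCM03 the same block reads "This training has helped me to see" and stops; in PCS00 it reads "This training helped me to think about" and stops. PCS01 to PCS05 are the same.

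The overall ratings on these nine forms, such as "Overall, what is your opinion of the training today", run from 1 = very good to 5 = very poor. The Appendix F form runs from 1 = poor to 4 = very good, with 5 = N/A.

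In the caregiver employment item of Appendix N, "1 = Peasant farmer" shares its code with teacher. Code 2 is both nurse and commercial farmer, and code 3 is both village health team member and alcohol brewer. In the position lists of Appendices R and U, code 15 is both volunteer and other.

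Section 5.7 promises piloting and refinement for Appendices U and V. No such provision is stated for the self-filled questionnaires or for Appendices N and R.

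**The concern.** A rating of agreement with a sentence that has no object carries no information. Trainees may supply an object of their own, repeat their previous answer or leave the item blank, and the analyst cannot tell which. The checklist on the front of each form asks trainees to confirm that every question was answered, so such ratings would probably be entered as data.

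These stems are the only closed items on the seven forms that refer to the content of the particular module. All six patient-centered services forms are affected, and Section 4.3 names the questionnaires as one of its sources for the process evaluation.

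The duplicated codes fail in another way. Double entry (Section 6.1.1) verifies that the code was keyed correctly, but it cannot say which of two occupations a 1 stood for. In an area described as very rural, one of the ambiguous options is likely to be common.

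**Working it through.** **Number of forms.** The plan's own figure comes first: (5 trainers + 30 staff) x 10 topics = 350, which matches Section 5.3.1. Table 5.1 gives the same number of topics: 3 (management) + 1 (fever) + 5 (patient-centered, clinical staff, counting parts I and II separately) + 1 (support staff) = 10. The printed trainee forms also number 3 + 1 + 6 = 10.

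**Unfinished statements, form by form.**

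| Trainee form | Skill statements unfinished |
|---|---|
| HCM01 | 0 of 5 |
| HCM02 | 0 of 5 |
| HCM03 | 5 of 5 |
| Fever case management | no such block |
| PCS00, 01, 02, 03, 04, 05 | 5 of 5 on each |

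The affected forms number 1 + 6 = 7, which is 7 of 10 trainee forms or 7 of the 9 with the common layout.

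The affected items number 7 x 5 = 35, out of 9 x 5 = 45 topic-skill items. Closed items per form are 9 + 5 + 5 = 19, so 5/19 = 26% are affected on each of the seven forms and 14 remain. Across the nine forms, 35/(9 x 19) = 35/171 = 20%.

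At the stated maximum, if all 30 staff attended every topic, up to 30 x 7 = 210 of 30 x 10 = 300 trainee questionnaires would carry the defect. This is an upper bound, because Table 5.1 sends different staff groups to different modules.

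**Is the cut-off an artefact of the file?** No. The text ends at the same word in all seven forms, while the two sister forms print the same stems with their objects.

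**Codes.** In Appendix N, 3 codes carry 6 occupations. The numbering looks like two lists merged: teacher, nurse and village health team as 1 to 3, and peasant farmer through transport as 1 to 6. The communication assessments allow up to 125 x 3 = 375 interactions, so up to that many forms carry the item. Code 15 in Appendix R affects at most 10 interviews, and in Appendix U at most 20.

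**Scales.** For fever codes 1 to 4, the matching label on the other forms has code 5 minus the fever code: 4 becomes 1 (very good), 3 becomes 2, 2 becomes 3, and 1 becomes 4 (poor). Fever code 5 is not a rating. The lowest category of the other forms, very poor, has no counterpart. The labels are printed on both forms, so the recode is determined.

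**The case against.** The strongest reply is that these are clerical slips on a small part of the instruments. Much of it stands.

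- A reader might infer that the forms as a whole cannot yield usable data. They can: on each affected form the nine learning statements, the five overall ratings and the comment boxes are complete.
- A reader might take these items to be the study's measure of dose received. No section says so. Section 4.3.1 defines that criterion as engagement with and use of materials, and draws on health center records, questionnaires, interviews and focus groups together. Appendix U, Part 2, asks module by module whether skills are used. It is only a partial substitute: it reaches up to 10 HFI health workers, targeted at in-charges, 9 to 12 months after roll-out.
- A reader might expect the opposite scales to reverse a cross-module comparison. Section 7.1 plans no such comparison. It assigns categorical questionnaire variables to chi-square or Fisher tests, which have no sign to reverse. Trouble arises only if raw codes, rather than labels, are combined. That some trainees would answer in the wrong direction is possible but conjectural.
- Code 15 is largely separable, because other has a write-in line and volunteer has none, and paper forms are kept. Appendix U is also to be piloted.
- Caregiver occupation is a descriptor that no objective uses, and Section 7.1 does not list the demographic form among its sources.

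None of this gives the 35 unfinished statements an object, or separates the paired occupations in Appendix N.

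**Conclusion.** The point holds in a limited form. As printed, 35 topic-skill items on 7 of 10 trainee questionnaires (7 of the 9 management and patient-centered forms) would be uninterpretable, as would employment codes 1, 2 and 3 in Appendix N. The loss is 5 of 19 closed items per affected form, not the form itself. Code 15 in Appendices R and U is minor, and the opposite fever scale is a risk only when raw codes are pooled across modules.

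The size assumes the forms are used exactly as printed. The figure of 210 questionnaires also assumes full attendance at every topic. The correction is worth making because no piloting is stated for these questionnaires or for Appendix N, and because neither the missing sentence endings nor the intended occupation can be reconstructed from the entered codes.

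**What to change.** Before printing:

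1. Complete the five stems on HCM03 and PCS00 to PCS05 from each module's topics and learning objectives, following the pattern of HCM01 and HCM02. The objectives on the matching trainer forms are a starting point, not a one-to-one source: PCS02 prints two, PCS00 three, and HCM03, PCS01 and PCS03 four each. Some stems will need wording from the topic list.
2. Give every employment option in Appendix N, and every position option in Appendices R and U, its own code.
3. Either align the fever form's scale with the other forms, or state that it will be recoded by form before any cross-module summary. Treat N/A as missing, under a code not already in use. It should not be 88, which means don't know on the study's other forms.

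The cost is reprinting the forms and notifying the review board of the new form version. The design, sample size and planned tests do not change.

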**Please write any comments on the above statements in this section here:**

**3. Please complete the table below about today's overall training by circling the response closest to your opinion.**

|                                                                  | Very good | Good | Fair | Poor | Very poor |
|------------------------------------------------------------------|-----------|------|------|------|-----------|
| What is your opinion of the trainer's skills today?              | 1         | 2    | 3    | 4    | 5         |
| What is your opinion of the trainer's attitude today?            | 1         | 2    | 3    | 4    | 5         |
| What is your opinion of the learner's manual you received today? | 1         | 2    | 3    | 4    | 5         |
| What is your opinion of the flip charts that were used today?    | 1         | 2    | 3    | 4    | 5         |
| Overall, what is your opinion of the training today?             | 1         | 2    | 3    | 4    | 5         |

**PATIENT CENTRED SERVICES**  
**SFQ for PARTICIPANTS – INTRODUCTION TO PCS & SOAs (PCS00)**

Health worker ID

[ ] [ ] [ ] [ ]

Today's date

[ ] [ ] / [ ] [ ] / [ ] [ ]  
day month year

